## Abstract

Patients feel more vulnerable when accessing community mental health programs for the first time or after being discharged from psychiatric inpatient units. Long wait times for follow-up appointments, shortage of mental health professionals, lack of service integration, and scarcity of tailored support can weaken their connection to the health care system. As a result, patients can present low adherence, dissatisfaction with treatment, and recurrent hospitalizations. Finding solutions to avoid unnecessary high-cost services and providing tailored and cost-effective mental health interventions may reduce the health system burden and augment patient support. We propose implementing an add-on, supportive text messaging service (Text4Support), developed using cognitive–behavioural therapy (CBT) principles to augment mental health support for patients attending to or being discharged from psychiatric care in Nova Scotia, Canada. This randomized controlled trial aims to investigate the effectiveness of Text4Support in improving mental health outcomes and overall mental well-being compared with usual care. We also will examine the intervention’s impact on health services utilization and patient satisfaction. The results from this study will provide evidence on stepped and technology-based mental health care, which will contribute to generating new knowledge about mental health innovations in various clinical contexts, which is not only helpful for the local context but to other jurisdictions in Canada and abroad that are seeking to improve their health care.

## 1. Introduction

Psychiatric patients may experience increased vulnerability during specific periods of their journey, especially when they first enrol in a mental health program or after being discharged from an inpatient unit [1,2]. Long wait times for follow-up appointments, shortage of mental health professionals, lack of service integration, and scarcity of tailored support can weaken the connection with the health care system for both newly admitted outpatients and those released from inpatient facilities [3]. As a result, patients can present dissatisfaction and low adherence to treatment, which may lead to undesirable outcomes such as mental health deterioration, increased readmissions, recurrent emergency department (ED) visits, and extended lengths of stay (LOS) during hospitalization [4,5]. Alleviating potential health distress and strengthening the patient’s connection with the health care service and provider can close the treatment gap experienced by many patients accessing or being discharged from formal mental health care services [6]. Moreover, delivering appropriate support and engaging patients with their treatment, especially when they feel vulnerable, are critical strategies for the effectiveness of mental health care and may positively impact health services utilization, preventing unnecessary high-cost health service use [6].

However, overcoming the gap in scaling up patient support should be not only evidence-based but cost-effective. One solution that meets these requisites is text message interventions. Short message service (SMS), commonly referred to as “text messaging,” is a service for sending short messages of up to 160 characters to mobile devices [7]. Even though this technology was developed more than 30 years ago, and even though it may be considered outdated in comparison to more cutting-edge technologies (e.g., mobile apps, augmented reality, etc.), text messages are now a part of the vast majority of people’s daily lives, becoming the most common and affordable communication function used on mobile phones, which is one of the reasons why they are still used to deliver virtual care in a significant portion of e-health services, including mental health and addiction programs (MHAPs) [8].

Text messaging technology has been proposed as a means to augment and extend the reach of mental health support [9,10]. Brief texting can be used as supportive text messages, social support engagement, care team contact capabilities, data feedback, psychoeducation, adherence-based psychotherapy, remote care delivery, medication adherance, and contingency management [11].

Cognitive–behavioural therapy (CBT), the standard of care for numerous mental health conditions, can also be delivered through text messaging programs [12]. Text4Mood and Text4Hope are two examples of such initiatives that have been successfully implemented in Alberta, Canada. Both programs have demonstrated that this innovation mitigates geographical limitations to access, offering a convenient and accessible means to provide mental health support for patients seeking psychological services as well as at the population level. Text messages were also to be found cost-effective since they do not require technical expertise, are free for end users, and only cost providers cents for each delivered message [13,14,15].

Two randomized controlled trials (RCTs) have also examined the efficacy of these interventions. The first one aimed to investigate the efficacy of supportive text messages in improving treatment outcomes in patients with major depressive disorder (MDD) [16]. For three months, the patients in the intervention group (*n* = 35) received twice-daily supportive text messages, whereas those in the control group (*n* = 38) received a single text message every two weeks, thanking them for taking part in the study. The Beck’s Depression Inventory-II (BDI-II) scores corrected for baseline showed a significant difference between the intervention and control groups at three months: 20.8 (SD = 11.7) vs. 24.9 (SD = 11.5), F (1, 60) = 4.83, *p* = 0.03, and *p*2 = 0.07, with an effect size (Cohen’s d) of 0.67. Similar differences (also adjusted for baseline scores) were observed between the intervention and control groups for the three-month mean self-rated overall health status scores (EQ-5D-5 and EQ-5D VAS): 65.7 (SD = 15.3) vs. 57.4 (SD = 22.9), F (1, 60) = 4.16, *p* = 0.05, and *p*2 = 0.065, with an effect size (Cohen’s d) of 0.51. These results indicate the potential value of supportive text messages as a psychological treatment for depression, particularly in underserved populations. The intervention was also found to reduce the psychological treatment gap, with 82% of respondents to a user survey reporting that the text messages made them more hopeful about dealing with issues in their lives. Additionally, 77% felt in charge of managing their depression and anxiety symptoms owing to the SMS messages, and 75% felt connected to a support network. The majority of the responders (83%) said Text4Mood enhanced their general mental well-being, supported their follow-up care (52.5%), and increased their sense of belonging (75.2%), all of which may have an influence on the demand for more intensive therapies [16].

Another RCT evaluated the effectiveness of Text4Hope, a CBT-based text message intervention deployed during the COVID-19 pandemic targeting the general population’s mental well-being [17]. The results from this trial indicated that receiving text messages for a brief period of time (six weeks) was effective in reducing stress, anxiety, and depression symptoms, as well as suicidal ideation in subscribers. The sum of the mean scores on validated scales such as the Perceived Stress Scale (PSS), the Generalized Anxiety Disorder-7 (GAD-7) scale, and the Patient Health Questionnaire-9 (PHQ-9) were compared. Subscribers who had received the messages for six weeks scored 20.9% lower than those who had recently subscribed to the program [17]. With >54,000 subscribers from March 2020 to July 2021, this emergency intervention proved to be scalable and significantly mitigated the need for readmission, a risk for COVID-19 infection, by reducing mental health distress by over 20% during the pandemic [18].

Text4Support is another text messaging program that offers mental health and addiction patients daily supportive text messages tailored to their diagnosis or most significant mental health concerns. The text messages have been developed by psychiatrists, psychologists, mental health therapists, and service users using CBT principles by focusing on the cognitive triangle of thoughts, feelings, and behaviours. The Text4Support suite of programs includes banks of messages, each of which is targeted to a specific concern: general well-being, depression, bipolar disorder, anxiety, psychosis, substance use disorder, personality disorders, and trauma-related disorders. A retrospective analysis of survey responses from individuals seeking access to mental health and addiction services (*n* = 296) enrolled in the Text4Support program for six months revealed that the text messaging intervention is a viable tool to complement existing programs and increase patient-system contact [19]. Another study used a combination of methods to assess user satisfaction with the Text4Support program [20]. Qualitative data collected from individual interviews and quantitative information extracted from web-based survey responses of the patients (*n* = 181) discharged from acute psychiatric care revealed that Text4Support was well received, with a high satisfaction rate for either message feedback or perceived impact. Furthermore, subscribers were pleased with the frequency of the messages, which were delivered once daily for six months. As a result of participant suggestions, the most recent version of the program includes separate text message banks targeting specific mental health disorders.

Although many studies [21,22,23,24,25,26] have shown that text messaging programs can improve the mental health of a varied population, when it comes to the specific diagnoses of psychiatric conditions and different levels of care complexity, the only data available come from pilot studies limited to patients diagnosed with depression and enrolled in outpatient clinics. This proposed trial primarily aims to close this evidence gap by providing fresh data on the efficacy of a CBT-based supportive text messaging program (Text4Support), compared with usual care, in improving transdiagnostic mental health outcomes among patients accessing different degrees of formal mental health care. Secondarily, we want to look at how the intervention affects the use of health services (crisis calls, ED visits, admissions and readmissions, and LOS following inpatient hospitalization) and patient satisfaction with mental health services (overall satisfaction, retention and withdrawal rates, and patient engagement). Lastly, we will explore Text4Support implementation outcomes (reach of the intervention, acceptability, appropriateness, fidelity, and cost-effectiveness). This research protocol will be helpful for any mental health services looking to enhance patient care and health services utilization while also extending support for those who need it. The findings of this study are expected to advance our understanding of mental health innovations in a variety of clinical contexts.

## 2. Materials and Methods

### 2.1. Study Design

This randomized controlled trial (RCT) is a multicenter, longitudinal, prospective, parallel, two-arm, rater-blinded methodology, with an embedded one-phase patient satisfaction qualitative sub-study and an implementation evaluation component. Hence, the study will have two groups (i.e., intervention group (IG) and control group (CG)), to which study participants will be randomized. The randomization process will employ permuted blocks, to ensure balance (1:1) between groups. To ensure allocation concealment, simple random allocation will be performed using a random number generator. The primary outcome measure for this study is transdiagnostic, with recruitment occurring in all mental health clinics and programs across the province, so stratified sampling will not be employed. Research team members working on the randomization and allocation processes will not be involved in the baseline and follow-up assessments. Data analysts will be blinded to treatment group allocation. Study subjects will, however, not be blinded since it is impossible to conceal which experimental condition they will be assigned to.

The qualitative sub-study on patient satisfaction will utilize qualitative descriptive methodology and thematic analysis [27]. We will select a purposive sample of the research participants to attend focus group sessions to uncover patterns or themes in the patient experience and satisfaction with the interventions. Finally, guided by the RE-AIM framework [28], we will evaluate the success of Text4Support implementation by looking at the intervention’s reach, effectiveness, willingness to adopt it, fidelity, and sustainability post-trial.

This protocol has been registered at ClinicalTrials.gov (NCT05411302) and approved by the Research Ethics Board for Nova Scotia Health (REB File#1028174). The trial will be carried out over three years, with 24 months dedicated to recruitment. The intervention will be delivered for 6 months, followed by an observation period of 12 months for each participant. The study flow diagram is represented in Figure 1.

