#### 2.4.4. Follow-Up Assessment

Participants in both study arms (intervention and control) will receive a link to the follow-up self-completed online surveys through SMS and be asked to complete them at 6 weeks and 3, 6, and 12 months after enrolment in the study. The same clinician-rated scales completed at enrolment will be completed over the phone by a trained research team member. A monitoring compliance strategy will be put into practice (a reminder text message after two days and then phone calls from the research team) in order to mitigate the loss of follow-up and improve patient compliance.

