### 2.5. Proposed Interventions

The intervention to be tested in this trial is the Text4Support program, which will be compared with a control condition. A day after enrolment, the participants randomized to the IG (Text4Support) will start receiving daily unidirectional (no-reply), CBT-based, diagnostic-specific supportive text messages for 6 months, as an add-on program to their usual care, with a subsequent observation period of 6 months, totaling 12 months of follow-up. Text4Support is powered by ResilienceNHope [34], an online application offered by the Global Psychological eHealth Foundation [35]. In action, Text4Support provides general content indicated regardless of the symptomatology presented, including messages of self-care, social support, hope, affirmation, and recovery (Figure 2a), as well as diagnostic-specific content focused on managing symptoms related to the diagnosis, such as the examples shown in Figure 2b,c. It is possible to observe the principles of the CBT cognitive triangle (thoughts, feelings, and actions) in the text messages shown, which is a key component of the program’s therapeutic effect. The text messages always encourage the recipients to consider their thoughts and feelings, and they suggest actions to take. The text message bank includes 180 messages per category (i.e., stress, mood disorders, anxiety disorders, depression, schizophrenia and other psychotic disorders, substance use disorders, adjustment disorders, and personality disorders). The messages were originally developed in Canadian English, and while the online application allows for translation into other languages such as French, Punjabi, Arabic, Ukrainian, Russian, and simplified Chinese, the proposed program will only be delivered in English. The program targets individuals who are receiving any type of assessment and/or treatment from mental health and addiction services. The subscribers can choose the bank of messages they want to receive based on their primary mental health concerns. The possibility of covering a wide range of mental health conditions, from the most to the least frequent and from mild to critical disorders, means that it can be used to augment mental health support for patients receiving various levels of mental health care in accordance with the project’s goals.

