The control condition comprises the standard care offered by each program/unit participating in this study (i.e., follow-up appointments or offering of community clinic/program treatment) and a single text message with the link to the e-mental health resources available on the NS Health MHAP website [36], following 12 months of the observational period. Currently, the NS Health MHAP website offers 22 freely accessible, evidence-based e-mental health tools covering a wide range of psychiatric conditions (i.e., substance abuse disorders, gambling, depression, anxiety, grief, bipolar disorders, eating disorders, obsessive–compulsive disorder, post-traumatic stress disorder, schizophrenia, and psychosis, among others), group ages (children, youth, adult, and seniors) and group identities (Black/African Nova Scotians, 2SLGBTQIA+, Canadian Forces, RCMP, caregivers and families, First Nations/Indigenous people, and first responders).

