### 2.6. Outcome Measures

The intervention effectiveness will be determined by evaluating the differences between the intervention and control group from baseline and the subsequent time points (6 weeks and 3, 6, and 12 months) for patient clinical outcomes and the differences between groups for health service utilization at 12 months, and the implementation success will be measured through quantitative and qualitative patient satisfaction data and implementation indicators, as follows:Clinical outcomes: The primary clinical outcome will be the differences in mean change in patient recovery and quality of life, assessed through the Recovery Assessment Scale (RAS) [37] and the World Health Organization Five Well-Being Index (WHO-5) [38]. Secondary clinical outcomes will include the differences between the intervention and control groups in prevalence changes for moderate-to-high depression (likely major depressive disorder), moderate-to-high anxiety (likely generalized anxiety disorder), and low resilience from the baseline to these time points, assessed through the Patient Health Questionnaire-9 (PHQ-9) [39], Generalized Anxiety Disorder-7 scale [40], and the Brief Resilience Scale (BRS) [41]. The mean score differences between groups from the baseline to determine time points will also be assessed using the Adverse Childhood questionnaire (ACE questionnaire) [42], and the Brief Substance Use Craving Scale (BSCS) [43], which will be used to assess childhood trauma and substance craving, as well as the clinician-rated Columbia-Suicide Severity Rating Scale (C-SSRS) [44], which will be used to assess suicide risk.Health service utilization outcomes: Health service utilization data will be extracted by the registration, reporting, and analytics, mental health and addiction team from the multiple health information systems utilized across NS Health and provided to the research team through reports. The differences in health service utilization data (mobile crisis visits, number of ED presentations, number of admissions in the last 12 months, length of stay, and the number of hospital readmissions) will be evaluated for participants in both groups. The differences between groups will be evaluated at 12 months.Patient experience and satisfaction outcomes: Patient satisfaction and patient experience with the e-mental health interventions (Text4Support and other e-mental health programs offered freely through NSH Authority) will be evaluated using both quantitative and qualitative data. Overall satisfaction will be assessed at each of the four time points (6 weeks and 3, 6, and 12 months) using a self-designed scale. Self-reported retention and withdrawal will both be assessed through the satisfaction survey, which addresses questions about the frequency of reading messages, the frequency of returning to messages stored in their phones, and actions taken by the participants after reading the text messages or freely available e-mental health resources (i.e., text “STOP”, clicking on links, searching for more information) up to 12 months after enrolment. Patient experience and satisfaction qualitative data will be collected through individual interviews and focus groups.Implementation Outcomes: Implementation outcomes are indicators of implementation efforts and are distinct from service or clinical outcomes [45]. For the intervention arm, we will include the reach of the interventions, acceptability, appropriateness, fidelity, and cost-effectiveness, evaluated at each of the four time points [28]. These implementation indicators will not be collected from the e-mental health or website visits in the control arm because they are not tied to the patient’s study ID and cannot be linked to the other measures.

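### Section 2.1 implies 18 months per participant where the rest of the protocol gives 12, and names two incompatible allocation methods, one of them offered as concealment

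*Protocol article*

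**What the plan says.** All references are to the protocol article.

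**Follow-up length.** Section 2.1: "The intervention will be delivered for 6 months, followed by an observation period of 12 months for each participant". Section 2.5, for the intervention arm, describes six months of daily messages "with a subsequent observation period of 6 months, totaling 12 months of follow-up". Section 2.4.4 has participants in both arms receive survey links and "be asked to complete them at 6 weeks and 3, 6, and 12 months after enrolment in the study". For health service use, section 2.6 says: "The differences between groups will be evaluated at 12 months". The last column of Table 1 is 12 months.

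**Total duration.** Section 2.1: "The trial will be carried out over three years, with 24 months dedicated to recruitment". Section 3 expects results within three years of project initiation.

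**Control arm.** Section 2.5 describes standard care and a single text linking to e-mental health resources, "following 12 months of the observational period". Section 2.6 surveys satisfaction, including with those freely offered resources, at 6 weeks and 3, 6 and 12 months.

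**Allocation.** Section 2.1: "The randomization process will employ permuted blocks, to ensure balance (1:1) between groups". The next sentence reads: "To ensure allocation concealment, simple random allocation will be performed using a random number generator". Section 2.4.3 places assignment after the baseline survey and otherwise refers back to section 2.1.

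**The concern.** Two statements in section 2.1 cannot stand beside the rest of the text.

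The first is the time each participant spends in the trial. Six months followed by twelve is eighteen, and nothing is scheduled for months 13 to 18 anywhere in the article. The figure matters for the end date and for what participants and sites are told about the length of their involvement.

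The second is how participants are allocated. Permuted blocks force near-equal arms at the end of every block, while simple allocation is a sequence of independent coin tosses with no such constraint. The two exclude each other. The sentence on simple allocation also treats generating the sequence as if it were hiding it. Concealment depends on who can see the next assignment before a participant is committed, not on how the numbers were drawn. Participants here are unblinded and both primary scales (RAS and WHO-5) are self-completed, so sound, concealed allocation is one of the main remaining protections against bias.

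**Working it through.** **1. Duration.** Inputs: recruitment of 24 months and total of 36 months (section 2.1); time per participant of 6 + 12 = 18 months (section 2.1) or 6 + 6 = 12 months (section 2.5, consistent with 2.4.4, 2.6 and Table 1).

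Last participant out = recruitment window + time per participant.

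| Reading | Calculation | Against 36 months |
|---|---|---|
| 12 months each | 24 + 12 = 36 | reproduces the stated three years |
| 18 months each | 24 + 18 = 42 | 6 months over |

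On the 12-month reading the slack is 36 − 36 = 0 months, while section 3 expects results inside the same three years. The remaining work includes extraction of administrative data from several systems (section 2.6) and an analysis starting from 100 imputed datasets (section 2.7).

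On the 18-month reading, finishing by month 36 would require enrolment to close at month 36 − 18 = 18. For 1500 participants that is 1500/18 = 83.3 per month, instead of 1500/24 = 62.5.

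**2. Control text.** Read literally, the phrase puts the single text after 12 months. The surveys on those resources would then begin at week 6, before the link had been sent. Read as a slip for *followed by*, it gives 12 months of observation after the text, which fits the survey schedule. The wording allows both.

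**3. Allocation and balance.** Input: at least 1500 enrolled (section 2.3). Under simple 1:1 allocation the difference in arm sizes has SD √N.

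- √1500 = 38.7, and 1.96 × 38.7 = 75.9.
- Arm sizes at the 95% limits: (1500 − 75.9)/2 = 712 and (1500 + 75.9)/2 = 788.
- Probability of an exact 750/750 split: about 2%.
- Efficiency loss at the limit: 1 − 4 × 712 × 788/1500² = about 0.3%.

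**4. Effect on power.** Section 2.3 states 131 per arm, 90% power, a difference of 2 (10 against 8) and two-sided α of 0.05. Taking 5 as the standard deviation, n = 2 × 25 × (1.960 + 1.282)²/2² = 131.3, which reproduces the stated figure up to rounding. Section 2.3 calls the 5.0 a variance; I use it as an SD here only because that is what returns 131.

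With 262 completers, √262 = 16.2 and 1.96 × 16.2 = 31.7, so the 95% limits are about 115 and 147. Power falls from 89.9% at 131/131 to 89.5% at 115/147.

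**The case against.** **The 18 months is one outlying sentence.** Every other section, and the sum 24 + 12 = 36, agree on 12 months. This stands. A reader might infer from section 2.1 that the trial cannot end in three years, but that follows only on the 18-month reading. The sentence is still wrong or contradictory as written, and only the sponsor can say which schedule was intended.

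**The lack of time for analysis depends on recruitment using all 24 months.** At the benchmark in section 2.3 (over 500 in six months, about 83 per month), 1500 would be reached in about 18 months, leaving roughly six. This also stands, so the point is conditional. The plan does nevertheless allot 24 months.

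**The service-use window is not in doubt.** Section 2.6 fixes the comparison at 12 months independently of section 2.1. I accept this.

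**The control phrase is probably a slip.** That is likely, given the surveys from week 6. A reader might infer that controls receive their link only after a year, but the documents do not establish it. The wording is ambiguous and needs correcting, no more.

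**Safeguards exist and detail may sit in the full protocol.** Section 2.4.3 puts assignment after the baseline survey, and section 2.1 keeps randomisation staff out of the assessments and blinds the analysts. Block size and central release are commonly left out of an article, so their absence is no finding. What remains is that the method stated is contradictory and the concealment statement is incorrect. The separation described is also from assessors, not explicitly from those who obtain consent and enrol.

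**Unstratified randomisation is valid at this size.** Agreed. Stratifying by entry route is a preference, not the correction of an error.

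**Conclusion.** The point holds as two contradictions in current text, both in section 2.1.

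- **Duration:** 18 months per participant against 12 elsewhere, which moves the end of follow-up from month 36 to month 42. On the 12-month reading the plan fits exactly, with no time for extraction and analysis if recruitment takes its full 24 months.
- **Allocation:** two mutually exclusive methods, with sequence generation offered as concealment. If simple allocation were used, the promised 1:1 balance would not be ensured (712 to 788 per arm at 1500).

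A reader might go further and conclude that the trial cannot be run as described. The documents do not support that. Either allocation method is workable, the choice costs less than half a percentage point of power, and it has no bearing on duration. The harm is an undefined procedure and an unsupported statement on balance and concealment.

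The duration figures are arithmetic on the article's own numbers. The power figures assume 262 completers, a difference of 2 and an SD of 5.

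**What to change.** 1. Reconcile the follow-up length across sections 2.1, 2.4.4, 2.5 and 2.6 and Table 1. Reword the control-arm sentence in section 2.5 so that the timing of the single text is unambiguous. Then restate the total trial duration and the expected results date in sections 2.1 and 3 to match, allowing time for data extraction and analysis.
2. Name one allocation method. Keep permuted blocks, with randomly varying block sizes, since they deliver the 1:1 balance that section 2.1 promises. Delete the sentence on simple random allocation.
3. Describe concealment in its own sentence: the sequence is generated centrally and withheld from those who consent and enrol participants until the baseline survey is complete. The last element builds on the order already given in section 2.4.3.
4. As an improvement rather than a correction, add entry route (new outpatient or inpatient discharge) as a covariate in the ANCOVA and the service-use models. It is known at enrolment, and Table 1 defines readmission by time since discharge, so it is tied to a stated outcome. Stratifying the randomisation by entry route is optional.

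The cost is protocol wording for items 1 to 3 and one extra model term for item 4, with no additional data collection. If recruitment has begun, the text should state the method actually in use.
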